### Objectives

To address this gap, we will test the impact of a yoga intervention on ER and pain severity and functioning compared to a general stretching or strengthening intervention. This design allows us to isolate the additional effects of yoga above and beyond more general movement practices, thereby testing ER as a key MOA underlying the clinical effects of yoga on CLBP. Specifically, we will test whether yoga’s effects on CLBP (improved pain severity and interference) are mediated by improved ER, the extent to which effects are related to specific aspects of ER, and the role of pain sensitization as a mediator or moderator of effects.

For the active comparison intervention, we chose to use stretching and strengthening exercises, given that we are interested in determining not only whether yoga influences ER but also the extent to which these effects are due to aspects of yoga above and beyond nonspecific factors (eg, expectancies, time, attention, and effort) [13] as well as improvements in strength and flexibility [4]. The 2 intervention groups will be similar in many aspects, but only yoga will incorporate aspects that we hypothesize will facilitate ER (eg, breathwork, mindfulness, and relaxation). We selected the hypothesized MOA based on our extensive work regarding the therapeutic characteristics of yoga and mechanisms of CLBP [5,14]. Our 3-month and 6-month follow-ups will allow us to examine whether the effects of yoga emerge later or persist. The study is highly innovative in its approach to testing the MOA of yoga for alleviating CLBP. By identifying the specific mechanisms through which yoga may influence pain, these results will facilitate optimizing interventions to improve therapeutic accuracy for prescribing and using yoga for CLBP, a highly prevalent and costly health condition in the United States and worldwide.

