### Ethical Considerations

The study was approved by the University of Connecticut IRB (#H19-191). Prior to completing any study procedures, all participants provide written informed consent on a form that was approved by the IRB at the University of Connecticut (IRB#H19-191). All study procedures are in accordance with the ethical standards described by the Helsinki Declaration. Study participants are assigned an identification number, allowing all stored records to be deidentified. Deidentified data are kept in locked file room or stored in a password-protected database on a password-protected computer. All participants are monetarily compensated for their participation up to US $400 for completing all study visits. Participants can withdraw from the study at any time.

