### Procedures

#### Randomization and Blinding

Eligible volunteers are scheduled to meet with a study staff member who will follow all informed consent procedures. After written consent is obtained, participants are randomized to the yoga or stretching and strengthening group using a stratified randomization scheme based on biological sex to ensure balance between groups, and the assigned group is known only by the study staff managing the participant and instructor schedules.

We will use blinding whenever possible. Assessments, evaluations, and data analysis will be conducted without the knowledge of participants’ assigned group. We will blind the study personnel to the assigned condition of subjects when conducting data collection by using unique study identification numbers, by following a strict script to refrain from discussing participant activities, and by using different members of the study team to coordinate assigned condition activities and collect data. Deidentified data with codes for assigned condition will facilitate blinded data analysis.

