### Exploratory Variables

Demographics, class attendance or home practice, expectancies, and substance use will be measured to examine the impact on the primary and secondary outcomes. A brief questionnaire (minimum data set as recommended by the National Institutes of Health Taskforce on Research Standards for CLBP) [54] will assess demographics (age, gender, race or ethnicity, education, and employment status) and medical or psychiatric history (comorbidities, medication usage, and ongoing treatments). Attendance at yoga or stretching sessions will be assessed using attendance data from the session recordings. The Essential Properties of Yoga Questionnaire [72] will be used to rate both interventions (yoga and stretching or strengthening) and measures the extent to which 14 different dimensions are emphasized in a mind-body intervention (eg, physical challenge, breathwork, restorative postures, and mindfulness). The Credibility Expectancy Questionnaire [73], a 6-item self-report instrument, will be used to assess treatment credibility and patient expectancy for improvement [74]. In order to assess participants’ use of tobacco, alcohol, prescription medicines, cannabis, and other nonprescribed substances, the Alcohol, Smoking, and Substance Involvement Screening Test [75] will be administered by study staff at each time point.

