### Statistical Analysis

The primary aim of this study will test the null hypothesis that the 2 population means are equal between the yoga and stretching and strengthening groups on the primary outcome, pain severity as measured by the BPI-SF, as well as the primary MOA, ER as assessed by the DERS. Power calculations incorporated prior effect sizes from works by others. A proposed sample size of 102 per group, which adjusted for attrition, was calculated to detect statistically significant results with 80% power (estimated *d*=0.50). In consideration of our secondary aims, we also powered the detection of paths a and b within pain interference mediation models. This was done using simulation in R (R Foundation for Statistical Computing; N=5000). Following simulation methods (N=5000) presented in Fritz and MacKinnon [76], sample size was determined by increasing simulation sample size until 90% of simulations significantly detected both paths a and b with estimated effect size magnitudes of *d*=0.39 (path a) and *d*=0.26 (path b) at α=.05. A proposed sample size of 116 was calculated, which was already reached when powering our primary aim.

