### Data Analysis

All analyses will be performed in SPSS (version 29; IBM Corp). A *P* value of .05 or less will be considered statistically significant. The primary outcome is pain severity (BPI-SF) and the primary MOA is ER (DERS). We will examine baseline demographics and study variables descriptively and test for differences between yoga and stretching and strengthening groups. If assumptions are met, a series of 2-sided *t* tests, mixed effects models, and path analyses will test our hypotheses. A mediation path analysis will be conducted examining the indirect path of group and change in ER from baseline to 6 weeks (path a), and change in ER from baseline to 6 weeks and pain severity (BPI-SF) at 12 weeks (path b) controlling for baseline pain severity. The magnitude of indirect path b will be assessed controlling for path a and the direct path between group and change in pain severity at 12 weeks (path c) to test if changes in ER predict subsequent changes in pain severity. Identical models will be created with change in ER from baseline to 12 weeks and pain severity at 3- and 6-month follow-ups. The magnitude of indirect path b will be compared between groups to test if the path between ER and pain severity is greater in the yoga group than in the stretching and strengthening group. If 95% CIs of path estimates do not contain 0, they will be considered meaningful. Finally, a series of moderated mediation path analyses will be conducted, examining the measures of baseline pain sensitivity (QST scores and normalized gene expression values), strength and flexibility, pain interference, and quality of life as moderators of the identical mediation model. All analyses will also be adjusted for important covariates including, but not limited to demographics (eg, biological sex, race, and sex), cohort, instructor, and intervention components (Essential Properties of Yoga Questionnaire) and credibility or perception of success (Credibility Expectancy Questionnaire). Sensitivity analyses will examine whether treatment responders and nonresponders differ significantly in baseline ER abilities. Baseline DERS scores will also be examined as a continuous moderator in main study analyses to establish whether some individuals may enjoy greater benefit from this intervention more than others.

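### Every analysis, including the primary arm comparison, is adjusted for a treatment credibility and expectancy score not fixed as pre-disclosure; if it is rated after participants know their arm, the adjusted coefficient no longer estimates the stated difference in means

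*Protocol article*

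**What the plan says.** The Data Analysis section lists t tests, mixed effects models and path analyses, and then states: "All analyses will also be adjusted for important covariates including, but not limited to demographics". The list goes on to cohort, instructor and ratings of intervention components, and ends with "credibility or perception of success (Credibility Expectancy Questionnaire". No model is exempted, so the sentence covers the 12-week BPI-SF severity comparison, the DERS comparison and path a (group to change in emotion regulation).

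The Exploratory Variables section says the CEQ "will be used to assess treatment credibility and patient expectancy for improvement". Its role there is exploratory: "expectancies, and substance use will be measured to examine the impact on the primary and secondary outcomes". Neither section says when the CEQ is completed, or whether it rates the assigned programme or both programmes.

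On sequence, Ethical Considerations says "Prior to completing any study procedures, all participants provide written informed consent", and Randomization and Blinding says "After written consent is obtained, participants are randomized to the yoga or stretching and strengthening group". The order of randomization and the baseline questionnaires is not given.

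The Statistical Analysis section gives the primary aim: to "test the null hypothesis that the 2 population means are equal between the yoga and stretching and strengthening groups". The Objectives explain the choice of an active comparator by an interest in effects "above and beyond nonspecific factors (eg, expectancies, time, attention, and effort".

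**The concern.** A covariate can be added safely to a randomized comparison when allocation cannot have affected it. A rating of how credible or successful a treatment seems is exposed to allocation as soon as the participant knows which treatment it is. If it is taken after classes begin, it may also reflect early improvement. Conditioning on such a score compares yoga and stretching participants with equal expectancy, and randomization does not make those subgroups comparable: optimism or early relief can raise both the CEQ and the pain result. The coefficient then answers a different question from equality of the two arm means.

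The primary pain result, the DERS result and path a are all at stake, and path a is half of the mediation claim. The distortion would be hard to notice. The CEQ varies between people within each arm, so the model fits without warning, and taking instructor and the yoga-component ratings out of the same covariate list would not remove it.

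**Working it through.** **Is the score post-allocation?** The article does not settle this. Pointing towards it:
- The CEQ rates a treatment, and the Data Analysis section describes it as perceived success.
- That section says baseline for pain severity, pain sensitivity and DERS, but not for the CEQ, which it lists beside instructor and delivered components.
- No section places the CEQ before allocation.

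Pointing away:
- Eligibility requires willingness to attend either programme, so both are known in advance and could be rated then.
- Randomization and Blinding says that only the scheduling staff know the assigned group, which leaves room for a rating after randomization but before disclosure.

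The arithmetic below therefore applies only if the score is taken after disclosure.

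**The plan's own figure.** With d = 0.50, two-sided α = 0.05 and 80% power, 63 per arm are needed (normal approximation) or 64 (t). Going from there to 102 implies attrition of 1 − 64/102 = 37% to 1 − 63/102 = 38%. No rate is stated, so 102 can be neither confirmed nor refuted, and this point does not depend on it. At 102 per arm before attrition, SE = √(2/102) = 0.140, 0.50/0.140 = 3.57, and power is 94.6%.

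**Effect of the adjustment.** Inputs: total effect 0.50 and 102 per arm (Statistical Analysis); δ and r assumed. The outcome is improvement, with within-arm SD 1 for outcome and CEQ.

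- Adjusted coefficient = 0.50 − δr
- SE = √(2/n) × √(1 − r²) × √(1 + δ²/4)

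For δ = 0.3, r = 0.3: coefficient 0.50 − 0.09 = 0.41; SE = 0.140 × 0.954 × 1.011 = 0.135; 0.41/0.135 = 3.04; power 85.9%.

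| δ (yoga minus control) | r | Adjusted effect | Power, 102 per arm |
|---|---|---|---|
| 0 | 0.3 | 0.50 | 96.3% |
| 0.2 | 0.3 | 0.44 | 90.6% |
| 0.3 | 0.3 | 0.41 | 85.9% |
| 0.5 | 0.3 | 0.35 | 72.0% |
| 0.5 | 0.4 | 0.30 | 62.1% |
| −0.3 | 0.3 | 0.59 | 99.2% |

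With an assumed 20% attrition (about 82 per arm), the δ = 0.3, r = 0.3 case has 77.7% power, against 89.1% unadjusted.

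**No true total effect, 102 per arm.** For δ = 0.3, r = 0.3 the coefficient is −0.09 and 0.09/0.135 = 0.67; the two-sided 5% test rejects about 10% of the time. For δ = 0.5, r = 0.3 it is −0.15 with SE 0.138, a ratio of 1.09, and about 19%. A simulation of one million records, in which CEQ and pain share only an unmeasured cause, gave adjusted effects of 0.41 and 0.35 and, under the null, rejection of 10.6% and 19.5%. With δ = 0 it gave no bias and 5.0%.

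The same formula applies to DERS and path a, with r the correlation of CEQ with change in DERS.

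**The case against.** - **Timing is unknown, and an article may leave it to the full protocol.** This stands in part. A reader might infer that the scores are certainly ratings of the assigned arm, made after allocation. The documents do not support that: they give neither timing nor target, and randomization after consent does not by itself make the score post-treatment. What remains is that the text admits a score taken after disclosure into every model.
- **The primary test may be an unadjusted t test.** A t test carries no covariates, and the sentence could mean adjusted versions in addition. But it is worded to cover all analyses. If the t test is meant to stand alone, the section contradicts itself and should say so.
- **Looking beyond expectancy is a stated aim.** It is, and the comparator controls expectancy fully only if both programmes are equally credible. But the Objectives offer the comparator as the control, and expectancy is classed as exploratory. That supports a mediator or sensitivity analysis, not a change to the primary contrast.
- **The harm is assumed.** Agreed: δ and r are illustrative. A reader might infer that power collapses, or that the 5% error rate is lost in any event. Neither follows. At 102 per arm the δ = 0.3, r = 0.3 case keeps power above the planned 80%, and the error rate is intact if the arms do not differ on CEQ.
- **Rejection at zero total effect may reflect a real direct effect** that expectancy offsets. That is so if the CEQ lies on the causal path. The 10% and 19% are false-positive rates for the total effect, which is what the stated null concerns. They are also false positives for a direct effect only if CEQ and pain are linked purely by common causes.

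**Conclusion.** The point holds in conditional form. As written, the plan adjusts the primary comparison, the DERS comparison and path a for a treatment rating that allocation can influence, and nothing restricts it to a score taken before disclosure. If it is taken afterwards and the arms differ on it, the adjusted coefficient departs from the stated difference in means by about −δr. At δ = 0.3, r = 0.3 that is 0.09 SD in either direction, depending on which arm is more credible, with about 10% rejection under no total effect. Larger assumed differences do more, and δ = 0 does nothing. The documents support no claim about the actual size or direction, since they contain no CEQ data.

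**What to change.** In the Data Analysis section:

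1. Exclude any CEQ score taken after allocation is disclosed from the models for the total arm effect (12-week BPI-SF severity, DERS, secondary outcomes) and from the path a equation. Only a rating made before disclosure may stay, as a baseline covariate. State when the CEQ is given and which programme it rates.
2. Address the expectancy aim with a labelled supportive analysis: CEQ as a mediator parallel to emotion regulation, or a CEQ-adjusted sensitivity model.
3. The CEQ may remain in the outcome (path b) equation as a mediator-outcome confounder. That equation also contains the group term, so say that its group coefficient is not the total or primary effect.

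The cost is a sentence or two of analysis text and one extra model, with no new data, visits or participants. The article plans no interim analyses and no analysis before final data collection, so on its account the change can precede any results. The small downside is that the primary estimate can no longer be described as net of expectancies; that claim moves to the supportive analysis.

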## Results

This project is funded by the National Center for Complementary and Integrative Health and reviewed by the University of Connecticut’s IRB. Recruitment began in September 2020. As of January 2024, we have enrolled 138 participants. We expect the study to be completed by May 2025. No interim analyses are planned for evaluation of the primary and secondary outcomes. Analyses will be conducted following final data collection using a mediation path analysis and series of moderated mediation path analyses to examine the mechanisms through which yoga reduces pain.

## Discussion

Yoga has been shown to decrease pain severity in individuals with CLBP. This study aims to determine whether ER is a mechanism of yoga through which a significant reduction in pain can be achieved. We will also determine whether yoga can lead to improvements in pain sensitivity, physical strength and flexibility, pain interference, and quality of life.

This will be the first study to assess ER as an MOA of yoga and interrogate plausible biological and psychological pathways that impact the contribution of ER on pain relief. The study results will provide empirical data on the role of ER as a MOA for yoga interventions and inform future studies on whether ER could be bolstered as a component of yoga or other mind-body interventions to improve pain outcomes.

Limitations of the study include that it will be performed at 1 site within the United States, and the interventions are only delivered in English. As a first step to determine whether ER is a MOA of yoga, the study may support evaluating or targeting ER in yoga interventions among more diverse populations, with delivery in other languages, and with other chronic pain conditions.

This 2-arm parallel group blinded RCT will examine ER as the MOA of yoga in individuals with CLBP. The study will provide important data for evaluating whether improvements in ER are responsible for reduced pain, whether pain sensitization moderates yoga’s effects on pain, or if yoga and improved ER abilities reduce pain sensitivity and thereby relieves pain. The study findings have important implications for future yoga research studies, as well as other mind-body modalities designed to improve pain management.

## Appendix

Multimedia Appendix 1 Peer-review report by the National Center for Complementary and Integrative Health (National Institutes of Health).

## Abbreviations

BPI-SF: Brief Pain Inventory-Short Form
CLBP: chronic low back pain
DERS: Difficulties in Emotion Regulation Scale
ER: emotion regulation
IRB: institutional review board
MOA: mechanism of action
QST: quantitative sensory testing
RCT: randomized controlled trial
REDCap: Research Electronic Data Capture
